### Safety Monitoring

Any patients with bleeding on dabigatran etexilate or warfarin therapy will be immediately hospitalized and screened for the severity of bleeding (mild, moderate, or life-threatening bleeding). The management of these complications will follow current guidelines and review articles [13-18].

All participants will have telephone visits scheduled weekly. After that period, study visits will be scheduled monthly. The telephone number of all the researchers will also be available to the patients. At any time, in any phase of the study, the patient will have the full right to request exclusion from the study.

*Electrocardiography* and laboratory tests (blood count, renal function, electrolytes, and liver function tests) will be performed monthly to monitor any changes that indicate bleeding or coagulopathy. Before the randomization and after the follow-up period, patients will undergo a brain computed tomography without contrast to exclude recent ischemic or previous hemorrhagic cerebrals events, and a transesophageal echocardiogram to check prosthesis function (including peak and mean gradient), and to check left atrial thrombus.

During the follow-up, if any unfavorable outcome with patients in the study is evidenced, an emergency meeting with the ethics committee will be held to evaluate the discontinuation of the study, regardless of their stage of recruitment. Other than that, every 2 months there will be a meeting with the same group with the intention of observing the progress of the study and the outcomes observed in each patient.

### Statistical Considerations

The SPSS 17.0 (SPSS Inc) will be used to perform statistical analysis of the collected data. The primary analysis will be performed according to the intent-to-treat principle. A safety analysis will be performed on all patients treated regardless of any protocol violations. The quantitative variables will be described as mean and standard deviation. The mean comparison will be performed by the Student *t* test for independent populations or related populations, as appropriate. The qualitative and categorical variables will be presented as percentages and their comparisons will be made by χ2 test (chi-square) or the Fisher exact test when indicated.

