**Conclusions:**

The study is in the recruitment phase. It is possible that dabigatran etexilate is as effective as warfarin in preventing the emergence of intracardiac thrombus in patients with AF and mitral and/or aortic bioprosthesis.

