### Randomization and Follow-Up

Prospectively, from August 2013 to April 2015, 100 consecutive patients between 18 and 64 years old, at least 3 months after mitral and/or aortic bioprosthesis valve replacement, documented AF postoperatively, and who match the eligibility criteria are being recruited from Ana Nery Hospital in Salvador-Brazil after obtention of informed consent.

For the allocation of the participants, a computer generated list of random numbers including 1 to 100 was used [12]. Following that, the allocation sequence was concealed (in sequentially numbered, opaque, black, sealed, and stapled envelopes) from the researcher who was enrolling and assessing participants. By convention, every “even number” is being allocated to the dabigatran etexilate group and every “odd number” to the warfarin group, that was consecutively selected blindly from the previous list, thereby selecting exactly 50 patients in each group (1:1 allocation), (Figure 1 shows this grouping). After this randomization, patients had study visits scheduled at 7 days (via telephone) and at 30 days (personally). The enrollment period was 21 months with a planned minimum follow-up period of 3 months.

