### Outcomes

The primary endpoint will be the appearance of an intracardiac thrombus in an esophageal echocardiogram to be held at the end of the follow-up. Other probable endpoints are the composite of stroke (ischemic or hemorrhagic), systemic embolism (to the central nervous system or peripheral), and prosthesis valve thrombosis. The safety endpoints will be any bleeding event (major or minor), elevated liver enzymes, or hepatic function abnormalities.

A thromboembolic event involving the central nervous system was defined as a sudden, focal neurological deficit of presumed vascular origin lasting 24 hours to 7 days (reversible ischemic neurological deficit) or enduring more than 7 days (stroke), as confirmed by computed tomographic or magnetic resonance scan imaging and evaluated by a skilled physician. A peripheral embolism was diagnosed when there was a sudden onset of arterial occlusion in the extremities (with or without cyanosis) and with reported absence of pulse, or sudden abdominal pain requiring urgent intervention (confirming acute intestinal ischemia during the surgical procedure). One of the criteria in the list below defined a major bleeding event [19]. All other bleeding will be considered minor and will also be computed.

Major bleeding criteria: (1) fatal bleeding, (2) symptomatic bleeding in a critical area or organ, such as intracranial, intraspinal, intraocular, retroperitoneal, intraarticular or pericardial, or intramuscular with compartment syndrome, and/or, (3) bleeding causing a fall in hemoglobin level of 20 g L^-1^(1.24 mmol L^-1^) or more, or leading to transfusion of two or more units of whole blood or red cells.

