## Results

Although the present study has no statistic power to proof non-inferiority, it is expected that the dabigatran etexilate group will be protected as well as the warfarin group from intracardiac thrombus, without increasing the bleeding rates, since we are using safer doses (110 mg bid). The lack of necessity of monitoring INR is also another factor that contributes to a better adherence to the new drug and it can make all the difference in the manner of doing anticoagulation for patients with similar clinical characteristics. Enrollment for this study started in July 2013 and is expected to conclude in April 2015. Final results are expected in September 2015. The study is in the recruitment phase.

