## Discussion

Anticoagulant treatment reduces the incidence of death and cardioembolic events in patients with AF or a prosthetic heart valve, and the incidence of death and recurrences in patients with venous thromboembolism [18]. Warfarin works by binding to vitamin K epoxide reductase to inhibit vitamin K-dependent coagulation factors II, VII, IX, and X. For all its extensive use, warfarin has many clinical shortcomings, including variable pharmacokinetic and pharmacodynamics properties, a narrow therapeutic index range, and numerous interactions with certain foods and drugs. All of these factors contribute to the need for frequent coagulation laboratory monitoring and dosage adjustments.

Recently, direct thrombin inhibitors and factor Xa inhibitors have been added to the armamentarium for anticoagulation in AF. Dabigatran is an oral, reversible, direct competitive inhibitor of thrombin, which prevents the conversion of ﬁbrinogen to ﬁbrin within the coagulation cascade, thereby inhibiting thrombus formation [8]. The association of AF and bioprosthesis increases significantly the thromboembolic risk, making the use of dabigatran etexilate uncertain at this scenario.  The RE-ALIGN trial [20] was the first clinical study to evaluate an oral direct thrombin inhibitor (dabigatran etexilate) as an alternative to warfarin for use in patients with mechanical heart valves requiring anticoagulation therapy. That study was prematurely interrupted because it showed increased rates of thromboembolic and bleeding events in the dabigatran etexilate treatment arm [20]. This report describes the rationale and design of the first clinical trial, to our knowledge, to test the hypothesis that dabigatran etexilate exhibits similar efficacy to warfarin with respect to prevention of intracardiac thrombus in patients with aortic and/or mitral bioprosthesis valve and AF postoperatively.

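### The Discussion says the trial tests similar efficacy on intracardiac thrombus, but the stated χ2/Fisher comparison at 50 per arm tests for a difference, and a non-significant result cannot support that hypothesis

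*Protocol article*

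**What the plan says.** **Aim.** The Discussion describes the first trial, to the authors' knowledge, "to test the hypothesis that dabigatran etexilate exhibits similar efficacy to warfarin with respect to prevention of intracardiac thrombus". The Objective in the Abstract is neutral: it speaks of examining the effect of dabigatran against warfarin.

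**Endpoint.** Outcomes states: "The primary endpoint will be the appearance of an intracardiac thrombus in an esophageal echocardiogram to be held at the end of the follow-up". This is a yes/no outcome per patient.

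**Analysis.** Statistical Considerations makes intention-to-treat the primary analysis. For qualitative and categorical variables it says that "comparisons will be made by χ2 test (chi-square) or the Fisher exact test when indicated".

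**Size.** Randomization and Follow-Up fixes 100 patients, 50 per arm, with a "planned minimum follow-up period of 3 months".

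**Status.** The Abstract calls the study an exploratory pilot. Study Design says that, as a pilot, it has no formal primary or secondary clinical outcomes. The Results section begins: "Although the present study has no statistic power to proof non-inferiority". The same sentence goes on to expect equal protection and no more bleeding. The Abstract's Conclusions say: "It is possible that dabigatran etexilate is as effective as warfarin in preventing the emergence of intracardiac thrombus".

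**The concern.** A χ2 or Fisher test asks whether the data are incompatible with equal risks. If it does not reject, the data may be compatible with equality, with moderate harm and with moderate benefit all at once. A hypothesis of similar efficacy needs the opposite form of evidence: an interval narrow enough to exclude differences that matter. The stated hypothesis and the stated comparison therefore do not fit each other, whatever the event rate.

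The article itself reports that a trial of dabigatran in patients with mechanical valves was stopped early for more thromboembolic and bleeding events. That is a different population from the bioprosthesis patients studied here. Still, it is a reason to show how large an excess the data leave open, which a p-value alone does not do.

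**Working it through.** **Inputs from the article.** 50 patients per arm (Randomization and Follow-Up); binary thrombus endpoint (Outcomes); χ2 or Fisher (Statistical Considerations).

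**Assumptions.** The article states no thrombus rate, significance level or margin. I take two-sided 0.05, complete data and a range of rates. The nearest figure in the article, 1%-4% per year, is for clinical thromboembolism, not thrombus on echocardiogram, so it does not fix the rate. There is no power calculation in the article to reproduce.

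**Step 1: what Fisher needs to reject.** Over all 2×2 tables at 50 v 50, the smallest imbalances with p<0.05 are 0 v 6 events (p=0.027), 1 v 8 (p=0.031) and 2 v 10 (p=0.028).

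**Step 2: power.** Power = Σ Bin(a; 50, p₁) × Bin(b; 50, p₂), summed over all tables (a, b) with Fisher p<0.05.

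| Assumed true rates | Ratio | Fisher power |
|---|---|---|
| 1% v 5% | 5 | 2% |
| 2% v 10% | 5 | 19% |
| 5% v 15% | 3 | 24% |
| 5% v 25% | 5 | 75% |
| 2% v 20% | 10 | 78% |

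The three five-fold rows run from 2% to 75%, so the base rate drives the answer. Uncorrected χ2 rejects more often (38% for 2% v 10%), but at low rates the expected counts are small and Fisher is the usual choice.

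**Step 3: what a non-significant result leaves open.** The Newcombe interval for d = p₁ − p₂ (dabigatran minus warfarin) uses each arm's Wilson limits (l, u):

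- lower = d − √[(p₁ − l₁)² + (u₂ − p₂)²]
- upper = d + √[(u₁ − p₁)² + (p₂ − l₂)²]

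*0/50 v 0/50.* The Wilson upper limit is z²/(n + z²) = 3.84/53.84 = 7.1% in each arm, and d = 0. The interval is −7.1 to +7.1 points.

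*3/50 v 0/50.* Fisher p=0.24. The Wilson limits are 2.06% to 16.22% and 0% to 7.13%, and d = 6 points.

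- lower = 6 − √[(6 − 2.06)² + 7.13²] = 6 − √66.4 = −2.1 points
- upper = 6 + (16.22 − 6) = +16.2 points

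*2/50 v 2/50.* Fisher p=1, and the interval is −9.9 to +9.9 points.

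Even identical event counts leave differences of 7 to 10 points open in either direction.

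**The case against.** The strongest reply is that the article already disclaims a confirmatory reading. It calls itself exploratory, says a pilot has no formal clinical outcomes, and concedes that it cannot prove non-inferiority. Its formal Objective is neutral, and the statements about equal protection are worded as expectation or possibility. The similarity hypothesis is one sentence in the Discussion. All of this stands, and it lowers the weight of the point. It does not remove the mismatch, because that sentence still says a hypothesis of similarity is being tested and the named test cannot do that.

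Three stronger readings are tempting and are not supported:

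- *A reader might infer that non-significance is almost guaranteed, even if dabigatran is several times worse.* That depends on rates the article does not give. Fisher detects 5% v 25% about three times in four.
- *A reader might infer that non-significance will be reported as similarity.* No section says so, and the power caveat points the other way.
- *A reader might fault intention-to-treat as the primary set for a similarity claim.* With no non-inferiority claim made, that choice is not an error.

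It is also fair to say that interval methods and further analysis sets are commonly left to a statistical analysis plan, which is not shown. The point does not rest on their absence. It rests on two printed statements that do not fit together.

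**Conclusion.** The point holds as a mismatch between the hypothesis in the Discussion and the comparison in Statistical Considerations. It holds at every event rate, because failure to reject equality is never evidence of similarity. The hypothesis also conflicts with the exploratory status and the stated lack of power for non-inferiority.

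Its practical size cannot be fixed from the article. With 50 per arm, two-sided 0.05 and no missing data, Fisher power over the assumed pairs ranges from about 2% (1% v 5%) to 78% (2% v 20%). The intervals do not need an assumed true rate, only an observed result: about ±7 points with no events, and −2.1 to +16.2 points for 3 v 0. This should be corrected before the final analysis. It does not invalidate the trial as a pilot.

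**What to change.** 1. In the Discussion, replace the statement that the trial tests similar efficacy with one that it estimates the difference in intracardiac thrombus between arms, for planning a larger trial. This brings it into line with the Abstract's Objective and the pilot label.
2. In Statistical Considerations, make the primary result the intention-to-treat risk difference in thrombus (dabigatran minus warfarin) with a two-sided 95% Newcombe interval. Report bleeding in the same form. Keep χ2/Fisher p-values as supportive only.
3. State that a non-significant p-value will not be reported as similar efficacy.

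The cost is a few lines of text and a short calculation, with no new patients or data. The real downside is that the trial gives up a similarity claim, which this design could not support. The interval and the Fisher p-value can also disagree at the edge: 5/50 v 0/50 gives p=0.056 with an interval of +0.9 to +21.4 points. Naming the interval as primary in advance settles which one leads.

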### Use of Concomitant Drugs

The use of drugs such as acetylsalicylic acid, clopidogrel, and other antiplatelet agents will not be allowed during the study period. The same applies to antiarrhythmic drugs that interact with dabigatran etexilate, such as quinidine.

## Results

Although the present study has no statistic power to proof non-inferiority, it is expected that the dabigatran etexilate group will be protected as well as the warfarin group from intracardiac thrombus, without increasing the bleeding rates, since we are using safer doses (110 mg bid). The lack of necessity of monitoring INR is also another factor that contributes to a better adherence to the new drug and it can make all the difference in the manner of doing anticoagulation for patients with similar clinical characteristics. Enrollment for this study started in July 2013 and is expected to conclude in April 2015. Final results are expected in September 2015. The study is in the recruitment phase.

## Discussion

Anticoagulant treatment reduces the incidence of death and cardioembolic events in patients with AF or a prosthetic heart valve, and the incidence of death and recurrences in patients with venous thromboembolism [18]. Warfarin works by binding to vitamin K epoxide reductase to inhibit vitamin K-dependent coagulation factors II, VII, IX, and X. For all its extensive use, warfarin has many clinical shortcomings, including variable pharmacokinetic and pharmacodynamics properties, a narrow therapeutic index range, and numerous interactions with certain foods and drugs. All of these factors contribute to the need for frequent coagulation laboratory monitoring and dosage adjustments.

Recently, direct thrombin inhibitors and factor Xa inhibitors have been added to the armamentarium for anticoagulation in AF. Dabigatran is an oral, reversible, direct competitive inhibitor of thrombin, which prevents the conversion of ﬁbrinogen to ﬁbrin within the coagulation cascade, thereby inhibiting thrombus formation [8]. The association of AF and bioprosthesis increases significantly the thromboembolic risk, making the use of dabigatran etexilate uncertain at this scenario.  The RE-ALIGN trial [20] was the first clinical study to evaluate an oral direct thrombin inhibitor (dabigatran etexilate) as an alternative to warfarin for use in patients with mechanical heart valves requiring anticoagulation therapy. That study was prematurely interrupted because it showed increased rates of thromboembolic and bleeding events in the dabigatran etexilate treatment arm [20]. This report describes the rationale and design of the first clinical trial, to our knowledge, to test the hypothesis that dabigatran etexilate exhibits similar efficacy to warfarin with respect to prevention of intracardiac thrombus in patients with aortic and/or mitral bioprosthesis valve and AF postoperatively.

## Abbreviations

AF: atrial fibrillation
CI: conﬁdence interval
DAWA: dabigatran compared with warfarin in patients with persistent or permanent AF after bioprosthetic mitral and/or aortic replacement
FDA: US Food and Drug Administration
INR: international normalized ratio
RE-ALIGN: randomized, phase II study to evaluate the safety and pharmacokinetics of oral dabigatran etexilate in patients after heart valve replacement
RE-LY: randomized evaluation of long-term anticoagulation therapy
RR: relative risk
VKA: vitamin K antagonists
